### Analysis strategy regarding moments of therapeutic interest and music technology

A qualitative data analysis serves to transcribe, identify, and code relevant and pivotal moments of the therapy and associate them with neural markers of emotional processing, following the procedures described in previous studies conducted by members of the research team [21, 22]. These moments will be referred to as moments of interest (MOI) and will be selected and identified to describe a narrative of the therapeutic change process and to analyze EEG event-related temporal dynamics during MOI as compared to moments of non-interest (MONI). More specifically, we plan to analyze the time-course of EEG power in alpha and theta frequency bands [22], which have been shown to be associated with emotional processing and neuropsychiatric symptoms [40, 41, 44]. By examining changes in these frequency bands in therapist-client dyads across sessions, we may obtain an indication of the underlying neural mechanisms involved in the therapeutic process. Observations from the therapist and a semi-structured interview will be utilized to select MOI by importance and emotional relevance. Participants may also report verbally any craving-related experience, which would also allow us to describe instances of neural dynamics of craving. MOI will be identified and located in the AV recordings of sessions. These reports and their timestamp of occurrence will be entered into a therapy event log. This semi-structured interview will also be conducted to explore participants' perspective and experience of using music technology in a music therapy intervention. HAQ-II will be completed by the IMT group and by the therapist after session 2 and 5 to graphically explore the dynamics of the therapeutic relationship and correlate with outcome measures. Audio–video recordings of individual sessions will be transcribed with ELAN [58] Version 6.2, Max Planck Institute for Psycholinguistics, Nijmegen, The Netherlands). MOI and MONI will be identified by the client, the music therapist and by an independent music therapist acting as a second rater. The analysis of interview responses and transcriptions of video recordings will be subjected to thematic analysis [57]. From this data themes will be identified pertaining (I) to participants' experience of MT in a CSMTS and (II) to participants’ experience of using music technology in MT. The research team will identify themes within the free text boxes of the post-MT questionnaires, satisfaction and exit surveys, and the discussions recorded within the focus groups. Audio recordings of the musical components will be analyzed using aural and spectral analysis while Musical Instrument Digital Interface (MIDI) data will be subject to computational analysis using the Music Therapy Toolbox (MTTB) [33].

## Discussion

### Expanding the music therapy research evidence base into community settings

The main reason to conduct this study is to report on the feasibility of implementing an MT intervention for SUD clients engaged with a CSMTS (five receiving IMT and five receiving GMT). Whilst the efficacy of MT for SUD has been suggested by previous research, there is a gap in the research literature concerning SUs engaged with CSMTSs [4, 6, 59]. This may be due to several reasons but – reflecting on our (DM, [name]) experience of working in community settings  CSMTSs may face unique challenges that are not often experienced in residential or private treatment centers. Some of the factors that can differ between interventions in CSMTSs and private/residential treatment services, include (I) SUs may have no contact with each other in-between sessions; (II) greater length between sessions; (III) larger opportunity for negative experiences between sessions; (IV) uncontrolled environment before and after sessions; (V) the commissioning process of substance misuse services can result in a change of quality and type of care where new providers are commissioned to provide the service; (VI) larger turn-over of staff; (VII) frontline staff with a higher caseload can result in less 1 to 1 time. However, it is worth highlighting some of the advantages of community over inpatient treatment: the main reason for community-based treatment is that it is open access (unlike inpatient, where the individual or local authority has to apply for and fund their stay). An additional advantage of delivering interventions in the community is it allows SUs to benefit from the effects of the intervention, techniques (such as managing triggers and cravings) and changes within their everyday environment. Delivering treatment within a community setting therefore removes one of the main risks of inpatient settings: discharge back to an environment which may be triggering and without techniques that have been tried and tested within such environments. They are receiving treatment in their natural environment which means they are putting skills such as managing triggers and cravings, into practice earlier on. Music therapy, we hope, will be another such support mechanism and given the current evidence base will assist to reduce craving and increase engagement in SUs [4].

### Craving and mental health

With the present study, we expect to report positive results regarding the feasibility of MT in CSMTSs that could benefit society through the development of MT intervention in community settings for SUD. This is especially important since, to date, there is no specific psychotherapeutic or pharmacological treatment to improve the mental health and reduce relapses in people with SUD demands [12, 25]. Results from this study may also help to provide more insight into outcomes related to co-occurring mental illness, a research target area set in a 2021 issued independent review from the UK’s Department of Health and Social Care [60]. Furthermore, primary results regarding the feasibility of MT for CSMTSs will influence the development of larger studies with appropriate, acceptable, and practical research procedures. As secondary purposes, this mixed-methods randomized controlled feasibility study aims at implementing a pretest–posttest methodology comparing MT in addition to ST vs ST alone on neurophysiological (EEG assessment) and questionnaire-based measures to provide novel and preliminary information concerning the effect of an MT intervention on craving and mental health-related clinical outcomes. In addition, qualitative measures regarding the therapeutic relationship as well as the application of music technology within MT will be explored. Therefore, the study will contribute to the existing literature regarding the feasibility of adopting such a mixed methodology in a CSMTS.

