**Methods:**

Fifteen participants, from a community service based in London, will take part in a mixed-methods non-blind randomized-controlled trial. Ten participants will receive six-weekly sessions of music therapy in addition to the standard treatment offered by the CSMTS—five of them will receive individual music therapy and five of them will receive group music therapy—while a further five participants will act as a control group receiving standard treatment only.

Satisfaction and acceptability will be evaluated in focus groups with service users and staff members following the final treatment session. Moreover, attendance and completion rates will be monitored throughout the intervention. Subjective and behavioral indexes will be assessed before and after the interventions to explore the effects of music therapy on craving, substance use, symptoms of depression and anxiety, inhibitory control, and will be correlated with associated neurophysiological signatures. In-session analysis of two individual music therapy sessions will serve to explore how music and emotion are processed in the brain within the therapy. The data collected at each step will be included in an intention-to-treat analysis basis.

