## Methods

### Study aims and specific objectives

The main aim of this study is to test the feasibility of implementing individual music therapy (IMT) and group music therapy (GMT) as an intervention for service users (SUs) experiencing symptoms of depression and/or anxiety and engaged with CSMTSs. In order to approach the primary aim, our objectives are (I) to measure qualitative data on SU satisfaction with the MT program, (II) to measure retention in treatment and (III) to collect their feedback over the course of the treatment. The secondary aims of this project are to examine the feasibility of applying a pre-test, posttest, and in-session assessment battery as well as to measure the effects of MT (GMT and IMT) on mental health and the neural processing associated with it. We aim to explore the effects of MT in addition to standard treatment (ST) versus standard treatment alone. Further secondary aims concern the exploration of features of the therapeutic relationship and the role of music technology in the delivery, recording, and analysis of music therapy sessions. In order to approach the secondary aims, our objectives are: (I) To measure the effects of MT in addition to ST on the following treatment outcomes in comparison to ST alone: (a) substance use, (b) physical, mental wellbeing and quality of life, (c) retention in treatment, (d) engagement with treatment, (e) completion rate, (f) emotional processing, (g) psychological symptomatology. (II) To measure reduction in craving intensity after single MT sessions. (III) To compare the effect of MT in addition to ST versus ST alone on craving, inhibitory control, depression, anxiety and the respective associated neural signatures. (IV) To explore the perceived therapeutic alliance in IMT sessions. (V) To explore the neural dynamics of emotional processing during IMT sessions. (VI) To explore SU experiences of using music technology in an MT intervention. (VII) To explore how music technology can be utilized in the subsequent analysis of audio data of musical interaction recorded during MT sessions.

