### Study design

Westminster Drug Project (WDP) is a substance misuse service provider delivering services within the UK. WDP’s Innovation & Research Unit (IRU) and the Cambridge Institute for Music Therapy Research (CIMTR), Anglia Ruskin University, have designed a mixed-methods feasibility study to address these aims and objectives. The study is designed as a three-armed study (Fig. 1) with group 1 receiving 6 weekly sessions of GMT alongside ST (see section “interventions”), group 2 receiving 6 weekly sessions of IMT alongside ST, and group 3 serving as a control group (CG), receiving 6 weeks of ST only. All participants will take part in pretest–posttest assessment (i.e., baseline and post-intervention measures) including subjective (i.e., multi-item questionnaires), behavioral (i.e., Go/No-Go task) and EEG measurements to assess several mental-health-related clinical endpoints. SUs allocated to group 2 will receive IMT while simultaneously EEG-hyperscanning is being recorded during the 2^nd^ and 5^th^ therapy sessions. After these two sessions, participants will undergo a semi-structured interview to select moments of therapeutic interest and complete a multi-item questionnaire measuring the quality of therapeutic relationship. Each participant allocated to GMT and IMT will also complete a single-item questionnaire to assess the intensity level of craving. Feedback from participants will be collected throughout the study and, where possible, requests will be implemented into the subsequent session. Engagement and treatment status of participants will be assessed 6 months post-intervention. After the intervention two different focus groups will be conducted: one involving MT participants and another involving a Staff Group (SG) of 4–8 WDP staff members who work with the service users involved. The SG focus group will explore the feasibility of MT from several perspectives, including those involved in the set-up of the MT sessions. Whilst the duration of the entire study is outlined to be a period of 3 months, participants will be committed for 8 weeks.

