### Analysis strategy regarding the secondary study aims

The strategy for the secondary aims entails data collection and analysis of quantitative and qualitative data from the EEG, questionnaires, a behavioral task, and a semi-structured interview. To analyze the effects of an MT program (GMT/IMT) in addition to ST compared to ST only on secondary dependent variables, descriptive, graphical, and inferential analyses will be used. Effect sizes will also be computed where relevant. The present research is a feasibility study and because of the small sample size, certain inferential statistics requirements cannot be satisfied. Therefore, results related to the secondary aims are to be considered—and will be presented as—preliminary. Descriptive analyses will be conducted by calculating means and standard deviations at each time point. Inferential statistical analyses will be conducted to evaluate the effect of MT (GMT/IMT) in addition to ST on mental health and brain processing by comparing the data between pre- and post- intervention in each group using a parametric or non-parametric test (e.g., paired t-test or Wilcoxon Signed-Rank test, respectively) depending upon the data distribution. The dependent variables that we will measure are pre-post intervention changes in the following outcomes: (I) score of the PHQ-9 and resting-state FAA for depressive symptoms; (II) score of the BSCS and resting-state beta frequency band for the craving state experienced over a 24-h period; (III) score of the GAD-7 and resting-state FMT for anxiety symptoms; (IV) score of the TOP for substance use, days of primary substance used, average usage of primary substance per day, physical wellbeing health, psychological health, and overall quality of life; and (V) P3 EEG event-related potential amplitude and behavioral accuracy during a Go/No-Go task for the inhibitory control. The statistical procedure to analyze data from pre-post intervention questionnaires involves both within-subject (or repeated-measures design) and between-groups (or independent design). Indeed, a pre-post intervention comparison of scores from the questionnaires will be performed for each group (GMT, IMT and ST) with a paired-samples t-test. In case the assumptions of normality and homogeneity of the data will be violated, a non-parametric Wilcoxon Signed-Rank test will be performed. The difference scores obtained from this repeated-measures design, will be used for the independent design analysis: pre-post intervention difference scores in the questionnaires administered to the MT groups (GMT and IMT) will be compared with pre-post intervention difference scores in the questionnaire administered to the ST group utilizing independent t-test. In case the assumptions of normality and homogeneity of the data will be violated, a non-parametric Mann–Whitney test will be performed.

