
For the resting-state EEG data (alpha—FAA -, beta, and theta—FMT—bands) pre-post intervention comparisons will be performed utilizing z-scores from a Normative EEG database (NG software) [54]. Furthermore, to represent the pre-post intervention difference in the topographic distribution of EEG power in the selected frequency bands a paired-samples t-test will be performed for each of the three groups. If deviations from normality will be found in the data, a non-parametric Wilcoxon Signed-Rank test will be performed. Between-group power differences will be calculated as well, by comparing differences in the topographic distribution of the EEG power in participants who received MT (GMT and IMT) alongside ST vs participants who received ST only through an independent t-test. If deviations from normality will be found in the data, a non-parametric Mann–Whitney test will be performed. Relationships between changes in the pre-post intervention questionnaire scores (PHQ-9, GAD 7, BSCS, VAS, HAQ-II) and changes in the respective EEG measures (see above) will be tested using Pearson's correlation coefficients with 95% confidence interval [16]. Likewise, we will implement the same correlation procedure to test the relationship between pre-post intervention changes in inhibitory control (P3 ERP amplitude and accuracy on “no-go” trials) and changes in the scores of the Brief Substance Craving Scale. Changes in the pre-post MT (GMT and IMT) sessions scores from the craving thermometer will be analyzed graphically (i.e., scatterplot). Those who attend more than two sessions but disengage before the study ends will have the measures up to the point of their disengagement included in data analysis.

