
## Conclusion

With this feasibility study we aim to lay the groundwork for researching MT interventions in CSMTSs, addressing a gap of research into mechanisms of change regarding craving and related mental health outcomes. We propose a mixed-methods approach created with feedback from service users and practitioners addressing clinical practice and research needs. The procedures have been adapted to clinical practice and with this small-N feasibility study we aim to create an empirical base for a larger-N RCT drawing on ‘different disciplines and bring[ing] practitioners and researchers together’ to find out ‘what works to combat substance misuse, across supply, prevention, treatment and recovery’ [60].

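### The planned MT-versus-ST comparison pools group and individual therapy, so each randomised format is reported only through uncontrolled pre-post tests; controlled by-format differences should be added beside it

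*Protocol article*

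**What the plan says.** All references are to the protocol article.

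- **Design.** Under Study design: "The study is designed as a three-armed study". The abstract gives the sizes: "five of them will receive individual music therapy and five of them will receive group music therapy", and "a further five participants will act as a control group receiving standard treatment only".
- **Comparative aim.** Under Study aims and specific objectives: "We aim to explore the effects of MT in addition to standard treatment (ST) versus standard treatment alone". The Discussion (Craving and mental health) repeats it: "comparing MT in addition to ST vs ST alone on neurophysiological (EEG assessment) and questionnaire-based measures". Neither sentence says how the two MT arms enter the comparison.
- **Between-group analysis.** Both tests are in the section on the secondary study aims. For resting-state EEG power the comparison is of "participants who received MT (GMT and IMT) alongside ST vs participants who received ST only through an independent t-test". For questionnaires, difference scores in the "questionnaires administered to the MT groups (GMT and IMT) will be compared with pre-post intervention difference scores" of the ST group, also by independent t-test. The fallback in both cases is a Mann–Whitney test.
- **Analysis by format.** The same section plans a paired test (or Wilcoxon signed-rank test) of pre-post change within each of the three arms. IMT and GMT are compared with each other only on feasibility measures, under the strategy for the main aim.
- **Status.** Secondary results are labelled preliminary, and the small sample is acknowledged.

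**The concern.** A three-arm randomised design gives each format a concurrent control. The written analysis uses that control only for the two formats combined. What it reports for each format separately is a within-arm change. Every participant enters with symptoms of depression and/or anxiety and receives ST, so that change mixes the format's effect with ST, time and regression to the mean. Readers interested in one format would find a p-value for uncontrolled change and no controlled difference beside it.

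The article itself gives a reason to look at the formats separately. Under Interventions it attributes to GMT benefits that arise between group members, such as cohesion and interpersonal learning, which one-to-one sessions cannot provide. If the formats differ in effect, the pooled estimate describes neither. The difference between them also enters the pooled test's residual variance.

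**Working it through.** **Inputs from the article:** three arms; IMT 5, GMT 5, ST 5 (5 + 5 + 5 = 15, matching the stated total). Under Recruitment, GMT may start with 3. The article gives no power calculation or effect size for this comparison.

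**Assumptions for illustration:** change-score SD of 1 in every arm, two-sided 5% level, effects from 0.5 to 2.0 SD.

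**1. Does the text pool?** The EEG sentence names one MT side and one ST side for one independent t-test, so it does. The questionnaire sentence, taken alone, could mean each MT group in turn. But where the section means arms separately it says so and lists all three, and the EEG sentence uses the combined form. Pooling is the natural reading.

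**2. What the pooled contrast estimates.**

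Pooled effect = (n_IMT × d_IMT + n_GMT × d_GMT) / (n_IMT + n_GMT)

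| IMT / GMT size | Share kept, effect in IMT only | Share kept, effect in GMT only | Share kept, equal effects |
|---|---|---|---|
| 5 / 5 | 5/10 = 50% | 5/10 = 50% | 100% |
| 5 / 3 | 5/8 = 62.5% | 3/8 = 37.5% | 100% |

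The weights follow recruitment, so what the pooled figure estimates shifts if GMT under-recruits.

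**3. Effect on the residual variance.** Take IMT 1.5 SD, GMT 0, five each. Each MT arm lies 0.75 from the pooled MT mean, which adds 10 × 0.75² = 5.625 to the expected sum of squares. Over 13 df that is 0.43, so the expected residual variance rises from 1 to about 1.43.

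**4. Power, as illustration only** (noncentral t; simulation with 40,000 runs for the one-format case).

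| Effect d | Pooled 10 v 5, both formats d | Separate 5 v 5 | Pooled 10 v 5, one format only |
|---|---|---|---|
| 0.5 | 14% | 11% | 6% |
| 1.0 | 39% | 29% | 10% |
| 1.5 | 72% | 55% | 15% |
| 2.0 | 92% | 79% | 18% |

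Pooling is better when the formats work equally and much worse when only one works.

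**5. Precision of by-format estimates.** SE = SD × √(1/n₁ + 1/n₂); half-width = t × SE. By-format contrasts come from one three-arm model with common residual variance.

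- At 5/5/5, pooled: √(1/10 + 1/5) = 0.548; 2.160 × 0.548 = 1.18 SD (13 df).
- At 5/5/5, each format v ST: √(1/5 + 1/5) = 0.632; 2.179 × 0.632 = 1.38 SD (12 df), about 16% wider. Analysed as an isolated 5 v 5 comparison (8 df) it would be 1.46 SD.
- With GMT at 3, pooled 8 v 5: √(1/8 + 1/5) = 0.570; 2.201 × 0.570 = 1.25 SD (11 df).
- With GMT at 3, GMT v ST: √(1/3 + 1/5) = 0.730; 2.228 × 0.730 = 1.63 SD (10 df), about 30% wider.

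**The case against.** The strongest reply is that the analysis answers the question asked. The comparative aim, the hypotheses and the expected results all concern MT as a class, and no format-specific efficacy aim is stated. The formats are kept apart in the main aim, which is feasibility, and there the plan does compare them. This stands: pooling does not contradict the stated aim, and the pooled contrast should remain.

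Three further points also stand.

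- A reader might infer that the trial cannot give a controlled estimate for either format. It can. Change scores are obtained in all three arms, so IMT minus ST and GMT minus ST follow directly. They are missing from the written analysis, not ruled out by the design.
- By-format estimates cannot choose a format. At 5 v 5 an IMT-minus-GMT interval has the same half-width of 1.38 SD as either contrast with ST. The Conclusion says "with this small-N feasibility study we aim to create an empirical base for a larger-N RCT", but the article does not say that effect sizes from this trial will feed that study's design, and the Discussion ties larger studies to the feasibility results.
- The extra attendance in IMT is not extra therapy. It is 2 × (115 − 60) = 110 minutes of EEG preparation and interviews, and both formats have six 60-minute sessions. It should not be used as evidence that the treatments differ.

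What the reply does not answer is that the plan already reports results by format, in their uncontrolled form. Imprecision is a reason to show wide intervals. It does not justify reporting within-arm p-values while leaving out the controlled difference.

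**Conclusion.** The point holds as a gap in the written analysis: the between-group comparison combines the formats, and each format on its own is reported only without a comparator.

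Its size depends on facts not yet known. With equal MT arms and no effect in one format, the pooled estimate is half of the other's effect. With GMT at three it keeps 62.5% of an IMT-only effect or 37.5% of a GMT-only effect. With a common effect nothing is lost and pooling is the more precise choice. It would therefore be wrong to say that pooling halves the effect in general. The power and interval figures rest on an assumed SD of 1, a common variance and no dropout.

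Importance is modest, because these outcomes are secondary, labelled preliminary and part of a feasibility study. The change is still worth making, since it needs no new data and analyses participants by the arms they were randomised to.

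**What to change.** In the section on the secondary study aims, keep the pooled MT-versus-ST contrast and state plainly that it combines the two formats, for questionnaires as well as EEG. Beside it, for the questionnaire, EEG and Go/No-Go outcomes, report the mean difference in change for IMT minus ST and for GMT minus ST, with 95% confidence intervals, from one three-arm model with common residual variance. Label these as descriptive and preliminary, and add no hypothesis tests for them.

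Two cautions belong with this. First, the recruitment text suggests that a single GMT group will run. If so, say that the GMT estimate cannot be separated from the effect of that particular group. Second, do not say that planning figures for the larger RCT will come from these estimates; five people per arm cannot support that.

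The cost is a few sentences and two contrasts per outcome. The intervals will be visibly wide: half-width about 1.38 SD against 1.18 pooled at 5/5/5, and about 1.63 against 1.25 for GMT versus ST if GMT has three.
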